###### Physical health check

Lung function as measured by spirometry (*CareFusion MicroLab* Spirometer); temperature; pulse; blood pressure; respiratory rate; oxygen saturation; electrocardiograph (*Philips Pager Writer TC70* Electrocardiograph Machine); and body composition analysis (fat-free mass, fat percentage, weight, BMI) using a *Tanita BC-420MA* Body Composition Analyzer (excluding participants with pacemakers/implantable defibrillators).

###### Six-minute walk test (^13^)

The distance walked in six minutes is a commonly used assessment of exercise capacity. The test is conducted in accordance with the guidelines provided by the American Thoracic Society (^13^). This and the following two measures are collected to better characterize the population and guide treatment. The six minute walk test is not repeated as we do not expect change in this measure with this intervention.

###### Mini Nutritional Assessment (^12^)

This six-item instrument is used to identify elderly patients (≥65 years) who are malnourished or at risk of malnutrition. Participants who screen positive for malnutrition (scores <12 U) are referred to the clinic dietitian.

###### Eating Assessment Tool-10 (^11^)

Swallowing difficulties are common in patients with COPD (^27^). The EAT-10 is a 10-item instrument used to assess the presence of swallowing difficulties. Patients with scores >3 U are referred for speech pathology review.

###### Hospital admissions and exacerbations

COPD exacerbation history is collected from participant self-reports for the 12 months pre- and postintervention. In addition, hospitalization and health resource use data are collected as detailed below.

### Cost-effectiveness data

We will evaluate health economic costs with an independent health economics researcher ([name]). The cost-effectiveness of adding the intervention to standard care for improving the HR-QoL will be investigated. Mean effectiveness and costs will be estimated from EuroQol-5 Dimensions-5 Levels (EQ-5D-5L) (HR-QoL); CRQ-Mastery subscale; nonpharmacological interventions (breathlessness pack as described above, action plan, clinic visits, home visits, telephone calls); outpatient visits; emergency department visits; hospitalizations; medication use; diagnostic and investigation use; and general practitioner visits.

Hospital and *Medicare Australia* data will be linked. Linked data from Centre for Health Record Linkage will be used to obtain health utilization data from the New South Wales (NSW) Admitted Patient Data Collection, NSW Emergency Department Data Collection, and NSW Ambulance Data. Inpatient stays will be costed using length of stay and case-mix weights for Australian Refined Diagnosis Related Groups (^28^). Outpatient clinic visits will be costed based on the Tier 2 Non-Admitted Care Services Classification (^29^) and emergency department visits using the urgency-related group cost weights (^29^). Medication and out-of-hospital services will be costed by *Medicare Australia* (https://www.humanservices.gov.au/customer/dhs/medicare). Costs associated with the intervention will be estimated as follows: hourly rates of local salaries plus on-costs for staff time; local reimbursement rates for travel costs; local hospital unit costs for the clinic; and the local hospital purchase price for equipment utilized for implementing the intervention (capital costs) and for consumables (handheld fan, telephone costs, pedometers, DVD, CD, patient handout folders).

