**FIG. 1. f1:**
[figure not shown]
Randomized-controlled trial design.

Participants are assessed before randomization and again eight weeks later. The standard care group is then offered the intervention. As a consequence, there are no control group data available for comparison beyond the eight-week mark. Primary and secondary quantitative assessments are re-evaluated three monthly after clinic completion up to one year. Once participants have completed the intervention, they are contacted by telephone by an independent interviewer ([name]). Details regarding the qualitative substudy are outlined in the analysis section of this article below.

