### Standard care group

Before randomization, all participants will receive standard care comprising correction of inhaler technique, printed handouts specific to current inhaler(s), a COPD educational pamphlet (http://lungfoundation.com.au/wp-content/uploads/2015/12/COPD_FS-Sep2015.pdf), a written COPD exacerbation action plan, and a pedometer. Current smokers will receive advice on smoking cessation. Participants in the standard care group are encouraged to utilize health resources as usual.

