### Cost-utility analysis

The primary outcome of the cost-utility analysis is the incremental cost per additional quality-adjusted life-year (QALY) at eight weeks, and the secondary outcome is the incremental cost per additional QALY at 12 months. Mean costs and effectiveness will be estimated from EQ-5D-5L; CRQ-Mastery scale; nonpharmacological interventions; outpatient visits; emergency department visits; hospitalizations; medication use; diagnostic and investigation use; and general practitioner visits. The mean incremental net monetary benefit will be estimated at potential threshold values for one additional quality-adjusted life year (^30^). Bootstrapping across 10,000 replicates will be conducted to robustly assess uncertainty for costs, effects, and cost-effectiveness, and cost-effectiveness acceptability curves will explore decision uncertainty (31, 32). Further sensitivity and scenario analyses will be undertaken to examine the effect of varying key parameter estimates on the outcome of the economic evaluation (^33^).

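### Pedometers are listed as an intervention cost although both arms receive one before randomization, so the eight-week incremental cost is overstated if the control arm's device is left uncosted (minor)

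*Protocol article*

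**What the plan says.** Standard care group: "Before randomization, all participants will receive standard care comprising correction of inhaler technique", and the list of items closes with "a written COPD exacerbation action plan, and a pedometer". Table 3 marks standard care as delivered to all participants before allocation.

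Cost-effectiveness data: the question is framed incrementally, "The cost-effectiveness of adding the intervention to standard care for improving the HR-QoL will be investigated". The costing rule then opens with "Costs associated with the intervention will be estimated as follows" and ends with items at the hospital's purchase price, including "consumables (handheld fan, telephone costs, pedometers, DVD, CD, patient handout folders".

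Cost-utility analysis: the primary economic outcome is defined as "incremental cost per additional quality-adjusted life-year (QALY) at eight weeks". A longer-horizon counterpart is also planned: "the secondary outcome is the incremental cost per additional QALY at 12 months".

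The device has two other uses in the article. Daily step count, a secondary outcome collected in both arms, is measured with it. The physiotherapist's entry in Table 2 bases walking programs on its readings.

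**The concern.** The comparator already contains the pedometer, yet the only place where the article prices one is under the intervention heading. An item held by both arms should cancel out of an incremental cost. Charged to one arm, it becomes a fixed amount per fast-track participant that the intervention did not cause.

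The primary economic outcome covers only eight weeks, so its QALY denominator is very small and a modest cost error becomes a large absolute change in cost per QALY. The planned bootstrap would not reveal it: the same amount is added in every replicate, so the whole distribution of incremental cost, and the acceptability curve with it, moves together. The trial's primary outcome, CRQ Mastery, is not affected.

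**Working it through.** The article states no pedometer price, incremental cost, QALY gain or cost per QALY, so there is no economic figure of its own to reproduce. The check has three steps.

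**1. Which arm holds the item**

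| Place in the article | What it shows |
|---|---|
| Standard care group | Every participant has a pedometer before randomization |
| Intervention (resources given at the first clinic) | Fan, DVD, CD, laminated action plans, handouts; no pedometer |
| Table 2, physiotherapist | Uses pedometer step counts; mentions no second device |
| Daily step count; Table 3 | Pedometer measures an outcome in all participants |
| Cost-effectiveness data | Pedometers priced under intervention costs |
| Cost-effectiveness data; Cost-utility analysis (other cost components) | Outpatient, emergency, hospital, medication, diagnostic and general practitioner use; none covers the standard care items |

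Nothing in the article suggests that fast-track participants receive an additional device.

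**2. Effect on the eight-week increment**

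Let c be the pedometer price, ΔQ the QALY gain at eight weeks, C the total incremental cost including the pedometer, and λ the threshold value of a QALY.

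- Costed in both arms or in neither: contribution to incremental cost = c − c = 0 (or 0 − 0 = 0).
- Charged to fast-track only: contribution = +c per participant.
- Net monetary benefit = λΔQ − C, so it falls by exactly c whatever the sign of ΔQ.
- Cost per QALY = C/ΔQ, so it rises by c/ΔQ if ΔQ > 0.
- Share of the ratio as costed = (c/ΔQ) / (C/ΔQ) = c/C. The small denominator cancels.

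**3. Illustrative size (all inputs assumed)**

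Price AUD 50-130; EQ-5D utility gain g reached linearly over eight weeks, so ΔQ = g × (8/52) / 2.

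| g | ΔQ | Shift at AUD 50 | Shift at AUD 130 |
|---|---|---|---|
| 0.03 | 0.0023 | 21,667 | 56,333 |
| 0.05 | 0.0038 | 13,000 | 33,800 |
| 0.08 | 0.0062 | 8,125 | 21,125 |

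Shifts are in AUD per QALY, from unrounded ΔQ. If the gain of 0.05 were immediate, ΔQ would double to 0.0077 and the shifts would halve to 6,500 and 16,900.

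For the share c/C, assume a total incremental cost of AUD 1,000-2,000. It then runs from 50/2,000 = 2.5% to 130/1,000 = 13%. At C = 1,000 and ΔQ = 0.003846 the ratio is 1,000/0.003846 = 260,000 with the pedometer. Without it, the ratio is 950/0.003846 = 247,000 or 870/0.003846 = 226,200.

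**The case against.** The costing sentence says how prices are obtained, not in which arm each item is counted. It never says that the control arm's pedometer goes uncosted, and the article's own definition of the question, adding the intervention to standard care, implies that a standard care item cancels. Allocation by arm is also a detail that a condensed article may leave to a fuller economic plan. This stands to the extent that the overstatement is conditional. It does not remove the inconsistency: the article prices the device only under the intervention, and no listed cost component would pick up the control arm's device.

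The device is also a real input to the walking program, so its cost matters wherever usual care does not supply one. That is fair, but it is a question about delivery elsewhere, not the within-trial comparison.

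Two stronger readings are tempting, and the article does not support them.

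- **That the 12-month ratio is overstated too.** Standard care participants are offered the intervention after week 8, and the Design section says that "there are no control group data available for comparison beyond the eight-week mark". A comparison of the randomized arms at 12 months would charge the pedometer to both, and no other comparator is defined. No direction of error can be claimed there.
- **That the error would dominate the economic result.** At an assumed AUD 50,000 per QALY, a gain of 0.003846 QALY is worth AUD 192, so a price of AUD 50-130 looks like 26-68% of it. That comparison ignores every other cost. The increment also carries physician, registrar and nurse time, home visits, calls and travel. With AUD 1,000 of incremental cost, the ratio lies far above 50,000 with or without the pedometer. The conclusion would change only if the other net costs happened to lie just below AUD 192, which nothing in the article indicates.

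**Conclusion.** The point holds as a minor inconsistency in the eight-week cost-utility analysis. The article places the pedometer in standard care for both arms and prices it as an intervention cost. On one condition, that the control arm's device is not costed, the incremental cost is too high and the net monetary benefit too low by exactly one pedometer price per fast-track participant. On the further condition of a positive QALY gain, the cost per QALY is too high by price/ΔQ.

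The first result is algebra and needs no assumed figure. The size in money rests entirely on assumption: about AUD 13,000-34,000 per QALY for a price of AUD 50-130 and a linear gain of 0.05, and roughly 8,000-56,000 when the gain varies from 0.03 to 0.08. The relative error is the price over the total incremental cost, probably small beside staff, clinic and travel costs. No claim is made about the 12-month ratio.

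**What to change.** In the Cost-effectiveness data section, remove pedometers from the intervention consumables, or state that they are costed identically in both arms. Add that items given to all participants before randomization, as listed under Standard care group, are excluded from the eight-week incremental cost. If the sponsor wants the cost of running the service where pedometers are not usual care, report it as one of the scenario analyses already planned under Cost-utility analysis. The change is one line in the costing plan and needs no new data.

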### Data analysis

Descriptive statistics of demographic information and spirometry will be reported. We will analyze data by intention-to-treat according to the original allocated group. As exacerbations of COPD, which increase breathlessness, may occur during the trial and therefore affect our primary outcome, we will also perform a per-protocol analysis to only include participants who have not had an exacerbation during the eight-week fast-track intervention standard care period. We will analyze all normally distributed, continuous outcomes with an analysis of covariance, adjusting for participants' baseline values. For non-normally distributed outcomes, we will use Poisson or negative binomial regression models, as appropriate. The proportion of participants achieving the MCID for each outcome measure will also be compared using a chi-square test.

The primary analysis will be adjusted for pulmonary rehabilitation completion in the last 12 months as per our randomization plan. We will then undertake analyses to assess whether specific variables are related to the outcome in models including the study intervention, followed by multivariable analysis to assess which are independent predictors of the outcome. Factors likely to be important in this analysis include modified Medical Research Council at baseline, use of long-term oxygen, the presence of a caregiver in the home, FEV1 at baseline, and CRQ mastery score at baseline.

The variables that are measured over time (i.e., at the start, at completion of the intervention, 3, 6, 9, and 12 months postintervention completion) will be analyzed using a general linear model to account for the correlation within a subject. Due to the few time points, whether the effect of the intervention is sustained will be investigated by assessing the average difference between time point and the baseline value using a Tukey's test to maintain the overall error rate.

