	Assessment of psychosocial issues.
	Introduction of nonpharmacological interventions such as handheld fan, breathing position and techniques, physical activity, energy conservation, relaxation, healthy eating, sleep, and if appropriate, anxiety and/or depression.
	Referral to external services as appropriate.
Physiotherapist	Education and practice of positions to ease breathlessness.
	Education and practice of breathing techniques.
	A variety of techniques have been described (^13^). We use the following techniques and definitions:
	Pursed lip breathing: inhalation through the nose and exhalation through pursed lips. This increases end expiratory pressure, preventing airway collapse and reducing end expiratory volume.
	Paced breathing: coordinates breathing with exertion. For example, walking up a stair is paced with respiration; the effortful part is paired with expiration.
	Recovery breathing: minimizes dynamic hyperinflation by prolonging expiration relative to inspiration. A rectangle (“breathe around the rectangle”) is used to help patients visualize this instruction.
	Controlled breathing: involves efficient breathing. Relaxation of the upper chest and shoulders is encouraged along with feeling the rise of the abdomen during inspiration.
	Education and practice of active cycle breathing technique to aid with sputum clearance if needed.
	Mobility and/or balance assessment if needed
	Prescription of walking aids if needed. Walking aids may be prescribed to assist with breathlessness management and/or to improve balance/mobility.
	Education about the deconditioning cycle and the benefits of physical activity.
	Development of a home exercise or walking program and/or referral to a community exercise program. As the intent of this intervention is to relieve breathlessness, rather than to provide pulmonary rehabilitation, exercise sessions will not be supervised. Walking programs are devised based on the participants step count as measured by a pedometer. Participants are given a program that aims to increase step counts by 10% each 1–2 weeks. Muscle strengthening programs, similar to those prescribed in pulmonary rehabilitation may also be suggested on an individualized basis.
	Education about the anxiety/breathlessness cycle.
	Review of relaxation training. Participants are reminded to use the provided relaxation CD.

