### Data collection

Outcome data are collected by research assistants not involved in delivering the intervention. Research staff involved in data collection are blinded. Primary and secondary outcomes are described in detail below. Table 3 describes the measures collected at various time points. In summary, data are collected at week 0 and 8 (face-to-face, in the patients' homes) to evaluate the quantitative outcomes. Patients allocated to the standard care group have data collected after completing the intervention (week 17). All participants have data collected at 3, 6, 9, and 12 months after completing the intervention by phone.

**Table 3. tb3:** Schedule of Enrollment, Interventions, and Assessments

Time point	Enrollment		Allocation	Postallocation																							Close out	
	−w 1	−w 2	0	W 1	W 2	W 3	W 4	W 5	W 6	W 7	W 8	W 9	W 10	W11	W 12	W 13	W14	W 15	W 16	W 17	W 22	W 30	W 35	W 43	W 48	W 56	W 61	W 69
Enrollment																												
Telephone screen	A																				F	S	F	S	F	S		
Informed consent		A																										
Standard care		A																										
Allocation			A																									
Intervention																												
Fast-track standard care				F	F	F	F	F	F	F	F	S	S	S	S	S	S	S	S									
				S	S	S	S	S	S	S	S																	
Assessment																												
Demographics		A																										
mMRC		A										A								S	F	S	F	S	F	S	F	S
CRQ		A										A								S							F	S
HADS		A										A								S	F	S	F	S	F	S	F	S
NRS		A										A								S	F	S	F	S	F	S	F	S
CAT		A										A								S	F	S	F	S	F	S	F	S
EQ-5D-5L		A										A								S							F	S
Height and weight		A										A								S							F	S
Step count				A								A								S								
Physical health check				F							F	S								S								
6MWT				F								S																
MNA				F								S																
EAT-10				F								S																
Hospitalizations		No. hosp. 1 year pre intervention																									No. hosp. 1 year post intervention	No. hosp. 1 year post intervention
Health care Utilization		A																									F	S

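### Table 3 takes the first step count at W1, after unblinded allocation, so the baseline-adjusted step-count comparison would condition on a value that allocation can affect

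*Protocol article*

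**What the plan says.** The Data analysis section states: "We will analyze all normally distributed, continuous outcomes with an analysis of covariance, adjusting for" each participant's baseline value. Outcomes that are not normally distributed go to Poisson or negative binomial regression.

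The Table 3 row for the outcome reads "Step count A A S". Counting columns, the entries are W1 (all participants), W9 (all participants) and W17 (standard care only). None stands in the two enrollment columns or the allocation column.

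The text differs. The Design section has participants assessed before randomization and again eight weeks later, and the Data collection section gives weeks 0 and 8.

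Under Standard care group, everyone receives, before randomization, items that include "a written COPD exacerbation action plan, and a pedometer". Under Daily step count, the value is the average over the preceding week, collected in clinic or by telephone. The physiotherapist's row of Table 2 says: "Participants are given a program that aims to increase step counts by 10% each 1–2 weeks".

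On lung function, the later predictor models list "FEV1 at baseline, and CRQ mastery score at baseline" among the candidate factors. The Physical health check section begins "Lung function as measured by spirometry", and the Table 3 row for that check reads "Physical health check F F S S": W1 and W8 in fast-track, W9 and W17 in standard care.

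**The concern.** Adjusting for a baseline value is safe because randomization guarantees that the covariate has the same expected value in both arms. That guarantee is lost once the covariate is measured after allocation, in participants who know their group. The Discussion accepts that participants cannot be blinded.

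W1 is also when the fast-track arm has Clinic 1: the six-minute walk test, the MNA and the EAT-10, all done at that visit, stand in the same column. Table 2 has the Clinic 1 clinicians introduce both physical activity and energy conservation, and the DVD given out there covers staying active. So advice bearing on steps does not wait for the physiotherapist.

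If any of this moves the W1 count in one arm, the adjustment transfers part of that movement out of, or into, the estimated effect. At stake is the between-arm comparison of a secondary outcome named in the abstract.

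**Working it through.** **Is the W1 entry a table-reading artefact?** Probably not. In the same table, CRQ, HADS, NRS, CAT and EQ-5D-5L all have their first entry in the last column before allocation. Step count alone among the outcomes compared between arms starts after it.

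**The plan's own figures.** The plan gives no effect, SD or correlation for step count. Its only planning figure is 56 per group for CRQ Mastery. With a difference of 0.55, SD 1.0, two-sided 0.05 and power read as 0.8, a t-test needs 53 per group, and 53/0.95 = 55.8, so 56. This reproduces, and the present point does not change it.

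**Formula.** Let D be the true between-arm difference at the final assessment, and f the fraction of D already present in the value used as baseline. Let ρ be the within-arm correlation of the two readings, with equal SDs, so that the ANCOVA slope is ρ. Then:

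- ANCOVA estimate = D − ρ·f·D
- share of the effect retained = 1 − f·ρ

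**Inputs for f.** These come from the protocol's 10% step each 1–2 weeks, compounded over eight weeks. I assume full adherence, no change in the control arm, and one step complete in the measured week.

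- Weekly steps: 1.1^8 − 1 = 1.144, so f = 0.10/1.144 = 0.087.
- Two-weekly steps: 1.1^4 − 1 = 0.464, so f = 0.10/0.464 = 0.215.

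**Assumed ρ.** 0.5 to 0.9; the protocol gives none.

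| f | Retained at ρ = 0.5 | Retained at ρ = 0.9 |
|---|---|---|
| 0 (pre-allocation value, or no early shift) | 100% | 100% |
| 0.087 | 1 − 0.044 = 96% | 1 − 0.078 = 92% |
| 0.215 | 1 − 0.108 = 89% | 1 − 0.194 = 81% |
| −0.1 (illustrative early fall) | 105% | 109% |

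A simulation with 200,000 participants per arm agreed with the formula to within 0.01 in every cell. The loss under the walking-program illustration is therefore about 4–19%. The sign reverses if early activity falls.

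**The case against.** The best defence is that the W1 reading may in practice precede any effect. Pedometers are issued before randomization, the count averages the preceding week, and a reading collected at Clinic 1 would cover days before intervention contact. The 10% program comes from the physiotherapist, after Clinic 1 and the team meeting, and is itself built on a pedometer count, so some count must come before it. This stands as a limit on direction and size: f may be near zero. It does not make W1 a pre-allocation value, since the protocol does not say which seven days the entry covers, and participants may already know their group.

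A reader might infer that the comparison is certainly biased toward no effect. The documents do not support that. It needs an early rise caused by the intervention, whereas Clinic 1 covers energy conservation as well as activity.

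A reader might also infer from Table 3 that baseline FEV1 is a post-allocation value, taken eight weeks later in standard care, and that it distorts the comparisons. That does not follow either. Spirometric FEV1 is an entry criterion in Table 1, and the Recruitment section allows results from the last 12 months where spirometry is paused, so a pre-randomization FEV1 exists in both arms. FEV1 is listed only for the later predictor models and cannot bias the step-count or primary comparison.

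Finally, ANCOVA applies only if step count is treated as normally distributed. That does not dispose of the point: a count model adjusted for the same W1 value would have the same weakness.

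**Conclusion.** The point holds in a limited form. Table 3 contradicts the Design and Data collection text on when step count is first measured. Read with the Data analysis section, it makes a post-allocation value the adjustment covariate for a secondary outcome. The direction of any bias is open: toward the null with an early rise, away from it with an early fall, and none if the measured week precedes any effect. The 4–19% loss is an illustration that rests on assumed correlations and on one full program step falling in the measured week; it is not an estimate for this trial. CRQ Mastery has a pre-allocation baseline and is not affected.

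On FEV1, only a clarification is due: the article does not say which FEV1 counts as baseline, and the scheduled health-check spirometry falls at different weeks in the two arms.

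**What to change.** 1. Reconcile Table 3 with the Design and Data collection sections: record the baseline pedometer week after the pedometer is issued and before allocation, and show it in the enrollment columns.
2. State that this value is the baseline covariate for step count in whichever model is used.
3. As a secondary clarification, state that baseline FEV1, in the predictor models and the descriptive tables, is the pre-randomization eligibility value in both arms and not the physical-health-check spirometry (W1 in fast-track, W9 in standard care).

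The cost is small but not nil. Table 3 puts consent and pre-randomization standard care, and hence pedometer issue, in the last column before allocation, and its enrollment week labels run in reverse order. The time available for wear is therefore not clear. Up to about one week may have to be added before allocation, and it must fit within the protocol's two weeks from baseline assessment to Clinic 1. Sample size does not change.

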### Measures

#### Outcome measures

##### Primary outcome measure

###### The CRQ—Mastery subscale (^15^)

The CRQ is a validated measure of breathlessness and related quality of life comprising four subscales dyspnea, fatigue, emotion, and mastery, each scored from 0–7, with higher scores reflecting better health. We will use the interview format, with readministration via the informed version. The MCID for each of the subscales is an increase of 0.5 U, with a change of 1 representing a moderate change and 1.5 a large change (^16^). This measure was chosen as we anticipate participants will exert to their maximum breathlessness, and thus, breathlessness intensity may remain stable. However, we hypothesize that participants will better tolerate breathlessness, and continue activities despite breathlessness but with increased mastery.

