##### Secondary outcome measures

###### The CRQ—Dyspnea, Fatigue, and Emotion subscales (^15^)

The dyspnea subscale is the average of five questions about breathlessness during activities. The fatigue subscale is an average of four questions about feelings of tiredness and energy levels, and the emotion subscale is the average of seven questions about emotional functioning. The MCID for each subscale is as stated above.

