###### Hospital Anxiety and Depression Scale (^17^)

The Hospital Anxiety and Depression Scale is a 14-item scale that measures anxiety and depression on separate subscales. It minimizes the use of somatic symptom items (e.g., loss of appetite) that may be confounded by patients' underlying medical conditions (^18^). The MCID for this instrument is 1.5 U for both the anxiety scale and for the depression scale (^19^).

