###### Breathlessness Numerical Rating Scales (^20^)

International guidelines recommend assessing both intensity and unpleasantness of breathlessness (^20^). Patients are asked to rate the intensity and the unpleasantness of their breathlessness after being at rest for 15 minutes on a 0–10 scale with 0 equating to no breathlessness/not unpleasant and 10 equating to maximal imagined breathlessness/maximal unpleasantness. Participants are also asked to report an activity that causes breathlessness, and report both the intensity and unpleasantness of this breathlessness. The MCID for this measure is 1 (^21^). In addition, participants are also asked to rate their confidence in managing their breathlessness from 0–10 with 0 equating to not at all confident and 10 to completely confident.

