###### EuroQol-5 Dimensions-5 Levels (^24^)

This is a standardized measure of health-related quality of life (HR-QoL) for clinical and economic appraisal. HR-QoL is measured across five dimensions: mobility, self-care, usual activities, pain/discomfort, and anxiety/depression with participants reporting the degree of problems in each area. A five-digit number describes health status across the five dimensions, and a weighted index value is derived. Overall health using a 0–100 visual analog scale ranging from worst health to best health is reported.

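### Every outcome judged non-normal, the primary included, is sent to a count model, although CRQ, HADS, NRS, CAT and EQ-5D are bounded scores or weighted indices and not counts

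*Protocol article*

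**What the plan says.** Two sentences of the protocol article's Data analysis section divide the outcomes by distribution. The first reads: "We will analyze all normally distributed, continuous outcomes with an analysis of covariance, adjusting for participants' baseline values". The second reads: "For non-normally distributed outcomes, we will use Poisson or negative binomial regression models, as appropriate".

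On the primary outcome specifically, the section adds only a covariate: "The primary analysis will be adjusted for pulmonary rehabilitation completion in the last 12 months as per our randomization plan". It does not fix the model family for the primary or exempt it from the second sentence.

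The Measures section describes the outcomes to which the rule applies:
- The CRQ subscales, including Mastery, are "each scored from 0–7, with higher scores reflecting better health". The secondary subscales are item means; for example, "The dyspnea subscale is the average of five questions about breathlessness during activities".
- HADS is a "14-item scale that measures anxiety and depression on separate subscales".
- The breathlessness NRS is rated "on a 0–10 scale with 0 equating to no breathlessness/not unpleasant".
- CAT runs from 0 to 40.
- For EQ-5D-5L, "a weighted index value is derived", alongside a 0–100 visual analog scale.

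Only exacerbations, hospitalizations and health service use are counts. Daily step count, reported as a weekly average, is arguably count-like.

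**The concern.** Poisson and negative binomial regression describe event counts. The Poisson model sets the variance equal to the mean, and the negative binomial sets it higher. A score confined to 0–7 with a mean near 4 and an SD near 1 has a variance well below its mean, so neither model describes it.

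The fallback also changes the question. The Sample size section plans a difference in mean change of 0.55 U, judged against an MCID of 0.5 U. A count model with the usual log link returns a ratio of means, and it cannot take change scores, which may be negative. A judgement about the shape of the observed data would therefore decide both the test and the effect measure of the primary comparison.

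**Working it through.** **1. The plan's own figure.** Inputs from the Sample size section: difference 0.55, SD 1.0, α = 0.05 (taken as two-sided), power read as 0.8, attrition 5%.
- Normal approximation: n = 2(1.96 + 0.842)² × 1.0² / 0.55² = 51.9, so 52; 52/0.95 gives 55.
- t-test: 52.9, so 53; 53/0.95 gives 56.

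The stated 56 per group reproduces. It rests on a linear comparison of mean change. With 53 evaluable per group, power is 0.80 by t-test.

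**2. Poisson standard error against the true one.** Take control mean m₀, intervention mean m₁ = m₀ + 0.55, n = 53 per arm and score SD 1.0. The Mastery mean is not in the article and is assumed.
- Poisson model SE of the log ratio: √(1/(n·m₀) + 1/(n·m₁))
- Approximate true SE: √(1/(n·m₀²) + 1/(n·m₁²))
- Power: 1 − Φ((1.96 × model SE − ln(m₁/m₀)) / true SE)

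At m₀ = 4, the model SE is √(1/212 + 1/241.15) = 0.0941 and the true SE is √(1/848 + 1/1097.2) = 0.0457, a ratio of 2.06. With ln(4.55/4) = 0.1288, power is 1 − Φ((0.1845 − 0.1288)/0.0457) = 0.11.

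| m₀ | Model SE / true SE | Poisson power |
|---|---|---|
| 3.0 | 1.80 | 0.24 |
| 3.5 | 1.93 | 0.17 |
| 4.0 | 2.06 | 0.11 |
| 4.5 | 2.18 | 0.07 |
| 5.0 | 2.29 | 0.05 |

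Under the null the rejection rate is below 0.001 throughout.

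**3. Simulation with baseline adjustment.** Settings: 53 per arm, effect 0.55, score SD 1.0, baseline correlation 0.5 (so change SD = √(2 × (1 − 0.5)) = 1.0, as planned), quarter-point scores limited to 1–7, 1,000 trials per cell. The item total is taken as four times the item mean; the article does not give the number of Mastery items.

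| Mastery mean | ANCOVA | Poisson, model SE | Poisson, robust SE | Poisson on item total, model SE |
|---|---|---|---|---|
| 3.5 | 0.891 | 0.138 | 0.896 | 0.847 |
| 4.0 | 0.894 | 0.076 | 0.900 | 0.823 |
| 4.5 | 0.891 | 0.038 | 0.899 | 0.761 |

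The item-total column averages (0.847 + 0.823 + 0.761)/3 = 0.81. A separate simulation at SD 1.0 gave about 88–90% for ANCOVA and 4–15% for Poisson with model SE. Across baseline SDs of 1.0 to 1.4, the ranges are 0.83–0.89 for ANCOVA, 0.04–0.14 for Poisson with model SE, 0.84–0.90 with robust SE and 0.73–0.85 on the item total.

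**4. Negative binomial.** Its variance is μ + αμ² with α ≥ 0, so the best it can do for underdispersed data is approach Poisson. With α near 0, mean 4 and baseline SD 1.2, power was 0.08, against 0.87 for ANCOVA in the matching cell.

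**5. Does non-normality require leaving ANCOVA?** With strongly skewed residuals and 53 per arm, ANCOVA's type I error was 0.04. At this sample size, skewness alone does not.

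**6. Scales with variance above the mean.** Assumed mean and SD: HADS 7 and 4, NRS 2.5 and 2.5, CAT 22 and 7. Baseline correlation 0.5, 600 trials each, so the simulation error near 5% is √(0.05 × 0.95/600) = 0.9 percentage points. Null rejection rates:

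| Scale | Poisson | Negative binomial | ANCOVA |
|---|---|---|---|
| HADS | 13.5% | 6.5% | 6.8% |
| NRS | 11.7% | 6.4% | 6.0% |
| CAT | 13.8% | 6.3% | 6.2% |

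A further run put negative binomial at about 3–6%. It behaves like ANCOVA here.

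**The case against.** The strongest reply is that the planned route for the primary is linear. The trial is sized on a mean difference, ANCOVA is named for normally distributed continuous outcomes, and nothing in the article shows that Mastery will be non-normal. The fallback has proper targets in admissions, exacerbations and service use, and the sentence may be compressed article text meant for those. The power loss also needs model-based standard errors and item-mean scoring; robust errors or the item total remove most of it. An analyst would probably notice the misfit: in one set of negative binomial fits to CRQ-like data, only 243 of 400 gave a usable p-value.

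Much of this stands, and it makes the harm conditional. It does not rescue the sentence. The stated trigger is non-normality, and the closing qualifier reads most naturally as a choice between the two count models. The article specifies neither robust errors nor item totals, and its 0–7 scoring points to the item mean. That the answer moves so far with the scoring unit is itself a reason not to use the model. Nor is this detail left to an analysis plan: the article states a rule, and a later plan would have to follow it or contradict it.

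A reader might also infer that standard errors would be too small for HADS, NRS and CAT. The document does not support that. It holds only if Poisson is chosen for overdispersed data, and the same sentence offers negative binomial, which keeps type I error near 5%.

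**Conclusion.** The rule is wrong as written because its scope is unrestricted: it sends bounded scores and weighted indices to count models and leaves the primary's model family to a data-dependent judgement. If Mastery were judged non-normal, the estimand would change from a difference in units to a ratio. Poisson with model-based errors on the 0–7 scale would have about 4–15% power against about 88–90% for ANCOVA, and negative binomial could not correct it. These figures assume a Mastery mean of 3.5–4.5, score SD 1.0 and 53 evaluable per arm. With robust errors (about 90%) or item totals (about 81%) most of the loss disappears.

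It would go too far to conclude that the primary test will be lost. That needs a finding of non-normality together with specific unstated choices, and the article gives no distribution for Mastery.

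**What to change.** Replace the fallback sentence with a rule by type of outcome:
- CRQ subscales, HADS, NRS, CAT and EQ-5D: ANCOVA on the baseline value whatever the distribution, adding the pulmonary rehabilitation stratum for the primary. Use robust or bootstrap confidence intervals if residuals are non-normal.
- True counts (exacerbations, hospitalizations, emergency department and GP visits): Poisson or negative binomial regression.

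Assign average step count to one of these groups by name. A proportional-odds sensitivity analysis for the scores is optional and not needed to cure the defect.

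The cost is one sentence in the analysis section or the analysis plan, settled before outcome data are examined by group. It needs no new data and does not change the sample size.
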